#### Cognitive capacity

Cognitive impairment is assessed with the Mini-Mental State Examination (MMSE) [74]. The MMSE contains 19 items and scores range from 0 to 30. For those participants who are not able to do one or more parts of the MMSE questionnaire due to issues unrelated to cognition, e.g. blindness, the total score is scaled. Participants unable to write are allowed to dictate the sentence. No reductions in scoring will be made because of this.

The Trail Making Test (TMT) is a widely used paper-and-pencil test to assess visual search, scanning, speed of processing, cognitive flexibility, and executive functions [75]. The test consists of two parts. In TMT-A, 25 encircled numbers are distributed on a sheet of paper, and the aim is to connect the numbers with a line as fast as possible (1–2–3-4-5, etc.). In TMT-B, the task is similar, except that the person must alternate between numbers and letters (1-A-2-B-3-C, etc.). If the participant makes an error, the examiner returns him/her to the last correct response immediately. The time required to complete each task is the participant’s score. The test result is disqualified if the time limit of 300 s is exceeded or four or more errors occur [76]. The TMT-A part assesses mainly visual search and motor speed skills, whereas TMT-B measures attentional control and cognitive flexibility [77–79]. B/A ratio of performance has been associated with executive functions [80].

Digit span test is a popular measure of auditory short-term memory, requiring the verbal recall of forward and backward number series, which the examiner says to the participant [81, 82]. The test starts with forward-series of four digits, and the string gets longer up to eight digits, until the participant fails twice. Then the same procedure is repeated, but the digits must be repeated backwards (from two to seven digit series). The score is the number of correctly repeated digit spans in both forward and backward tests (maximum 17). The forward digit span relies on the phonological loop of working memory, whereas the backward digit span also engages the central executive component [83].

Digit symbol coding task is a paper-and-pencil test measuring processing speed and short-term visual memory (The Wechsler Adult Intelligence Scale-Revised) [84] . The participant has to draw correct symbols below their equivalent numbers by using a number-to-symbol coding key. Time limit of the task is 90 s, and the score is the number of correct symbols in correct order (maximum 65). Several abilities are needed to perform well in the task, and scores have been found to decline steeply with age [85, 86].

Phonemic verbal fluency is measured with a modified, version of Word Fluency [82, 87]. In the test, participants are instructed to name as many Finnish words as possible, starting with the letter K, during 3 min (instead of the original 5 min). The examiner writes down the words said by the participant, and the score is the number of acceptable words (including a limited number of names). Verbal fluency test measures semantic memory and verbal ability, and it is a sensitive indicator of brain dysfunction, because the task requires both clustering (certain phonemic category) and the ability to shift efficiently to a new strategy [88].

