Reaction time and sensory motor speed are assessed first with a simple finger movement task, followed by a complex finger movement task [59]. The seated participant holds index finger of the dominant hand resting on the rest button in the middle. The participant will move the finger as soon as possible to the button closest to the light, when it switches on. First, the simple reaction time test is conducted and then a more complex test, where any of the seven lights switches on randomly. Reaction time and movement time are measured in milliseconds. The simple and complex tasks are each repeated 12 times. The average times of the final five correctly performed tasks will be used as the result.

Lower-extremity physical performance is objectively assessed in the participant’s home by the Short Physical Performance Battery (SPPB) [60–62]. The battery comprises tests on standing balance, walking speed over a 3-m distance, and the ability to rise from a chair. Each task is rated from zero to four points according to established cut-off points [61, 62], higher scores indicating better performance. Participants unable to perform a test due to mobility-related limitations will be assigned a score of zero for each respective test. A sum score will be calculated (range 0–12), when at least two tests are completed.

Ten-meter walking speed is assessed in the laboratory corridor. The time to walk ten meters with habitual and maximal speed is measured using photocells (Faculty of Sport and Health Sciences, University of Jyvaskyla, Jyväskylä, Finland) and a hand-held stopwatch (for cohort comparisons) and walking speed expressed in m/s will be calculated. On their first walk, participants are instructed to walk at their habitual speed, that is, the speed they would use when running errands [63]. On the second walk, participants are instructed to walk as fast as possible, without compromising safety, for the maximal test [64]. In both tests, five meters is allowed for acceleration, and the walking stops well past the finish line. Participants wear walking shoes or sneakers and are allowed to use a walking aid if needed. The test-retest precision of the maximal walking test with a one- to two-week interval has been shown to be good in our research center [65].

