Hearing acuity. Participants are asked about use of hearing aids. Self-rated hearing is assessed using a question “How is your hearing?”, and it is answered by choosing a number along a continuum between zero (very poor) and ten (very good). Participants using hearing aids evaluate their hearing with and without the aid. In addition, participants are asked whether they are able to hear in a normal conversation with three or more persons with response options: one (yes, without difficulty), two (yes, with some difficulty), three (yes, with a great deal of difficulty), and four (no, not at all). Pure-tone screening audiometry (Oscilla USB-330, Inmedico A/S, Denmark) and Peltor noise reducing headphones with a noise reduction rating of 21 dB are used to measure pure-tone air-conducted hearing thresholds [71]. Hearing thresholds are estimated using the automatic Hughson-Westlake protocol at the frequencies of 0.125, 0.25, 0.5,1, 2, 4, and 8 kHz. Both ears are measured separately. The maximum sound intensity is 90 dB. If the participant does not hear at an intensity of 90 dB, 100 dB is recorded as the hearing threshold.

Visual acuity. Self-rated vision is assessed by asking about the use of spectacles, and if yes, what kind of spectacles with response options: one (reading glasses), two (glasses for farsightedness), three (glasses for reading and farsightedness), four (multifocal glasses), and five (other). Near vision is assessed by asking whether the participant is able to read normal newspaper text. Far vision is assessed by asking whether the participant is able to watch television from a normal watching distance (three meters). The response options are: one (yes, without difficulty), two (yes, with some difficulty), three (yes, with a great deal of difficulty), and four (no, not at all). Binocular visual acuity is assessed first without and then with the participant’s own spectacles. Illuminated Landolt ring chart (Oculus 4512) at a 5 meter distance is used for assessment. The Landolt rings are widely accepted as the standard of reference in measuring distance visual acuity [72].

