### Statistical analyses

Non-respondent analyses will be conducted to determine differences between participants in different parts of the AGNES study and those not participating in the respective parts in order to establish potential selection bias.

Full information maximum likelihood (FIML) estimation under the assumption of data missing at random (MAR) will be used in analyzing incomplete data. Multiple imputation methods will be used to complete the dataset for efficient and valid analyses. In sum score calculations, limited numbers of missing items (e.g. one or two), will be imputed with the participant’s mean of completed items (scaling), while in some cases best available information may be used to replace missing values.

The study data to be collected will consist of a cross-sectional dataset. Path modeling and structural equation modeling will be used for multilevel analyses of environmental and individual characteristics relative to the study outcomes. The cross-sectional data will be analyzed with Bayesian methodology permitting better control of expectations generated by previous research, and interpretability of the results. Markedly non-normally distributed data will be transformed prior to inferential comparisons. For variables that cannot be successfully transformed, nonparametric methods will be used. Categorical variables will be analyzed with logistic regression or categorical response models. If the expected frequencies are too small for asymptotic assumptions, exact testing techniques will be used.

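### Trail Making time-outs are disqualified and no other value is assigned, so an analysis under missing-at-random discards the known fact that the time exceeded 300 s and understates mean time and spread

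*Protocol article*

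**What the plan says.** Under Cognitive capacity, the article defines the TMT score for parts A and B by completion time: "The time required to complete each task is the participant’s score". Errors are corrected while the test is running: "If the participant makes an error, the examiner returns him/her to the last correct response immediately". The rule at issue comes next: "The test result is disqualified if the time limit of 300 s is exceeded or four or more errors occur". A source is cited for it, but the text does not say how a disqualified result is coded.

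Under Statistical analyses: "Full information maximum likelihood (FIML) estimation under the assumption of data missing at random (MAR) will be used in analyzing incomplete data". It adds: "Multiple imputation methods will be used to complete the dataset for efficient and valid analyses". Neither sentence makes an exception for tests failed through poor performance. The only flexible wording comes in the sentence on sum scores: "while in some cases best available information may be used to replace missing values". It is not tied to the TMT.

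Two other performance measures keep the poorest performers in the data. For the SPPB: "Participants unable to perform a test due to mobility-related limitations will be assigned a score of zero for each respective test". For audiometry: "If the participant does not hear at an intensity of 90 dB, 100 dB is recorded as the hearing threshold".

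**The concern.** MAR allows missingness to depend on what was observed, but not on the missing value itself once the observed data are taken into account. A TMT result removed for exceeding 300 s is removed because of its own size. It is also only partly unknown: the time is known to lie above 300 s. A MAR analysis ignores this and places most time-outs back inside the range that they are known to have left.

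Functional abilities are predictors of active aging in the first project aim, and the sample is aged 75, 80 and 85. If time-outs become more common with age, the distortion differs between age groups, and age differences in TMT performance are understated. The B/A ratio is affected too, since it is lost whenever either part is disqualified.

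**Working it through.** The documents state no figure to reproduce. The check sets the two rules side by side and then illustrates the size.

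**Logic.** Let T be the completion time. The time rule makes T unavailable exactly when T > 300 s. The planned analyses model T from the other observed variables among people with T ≤ 300 s and apply that model to those with T > 300 s. Other cognitive tests in the model reduce the error but cannot remove it.

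**Assumed inputs (none is in the article).** Log T is normal with SD σ = 0.45. The median m is 140, 180 or 220 s; these are scenarios, not estimates for the three ages. The standardized slope of the outcome on log time is −0.30. One auxiliary variable correlates 0.3, 0.5 or 0.7 with log time. The four-error rule is not modelled.

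**Formulas, with c = ln(300/m)/σ:**
- share over 300 s: q = 1 − Φ(c)
- true mean: m·exp(σ²/2)
- complete-case mean: true mean × Φ(c − σ)/Φ(c)
- mean of the time-outs: true mean × [1 − Φ(c − σ)]/q

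**Worked for m = 180 s.** c = 0.5108/0.45 = 1.135, so q = 12.8%. True mean = 180 × exp(0.10125) = 199 s. Complete-case mean = 199.2 × 0.7533/0.8718 = 172 s. Time-outs truly average 199.2 × 0.2467/0.1282 = 383 s.

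**Simulation (1,000,000 draws per setting).** Times over 300 s are deleted and then imputed by stochastic regression on the outcome and the auxiliary variable. Ranges run over the three auxiliary correlations.

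| | m = 140 | m = 180 | m = 220 |
|---|---|---|---|
| Share over 300 s | 4.5% | 12.8% | 24.6% |
| True mean (s) | 155 | 199 | 244 |
| Complete-case mean (s) | 145 | 172 | 192 |
| MAR-imputed mean (s) | 146–149 | 175–181 | 196–207 |
| SD of log time under MAR, relative to true | 0.91–0.93 | 0.82–0.85 | 0.74–0.77 |
| Correlation, complete case (true −0.30) | −0.27 | −0.25 | −0.23 |
| Correlation, MAR | −0.28 to −0.29 | −0.26 to −0.29 | −0.23 to −0.28 |
| Slope, complete case (true −0.30) | −0.30 | −0.30 | −0.30 |
| Slope, MAR | −0.31 to −0.32 | −0.31 to −0.34 | −0.32 to −0.36 |
| Slope, time-outs set to 300 s | −0.31 | −0.33 | −0.36 |

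Across the three scenarios, 76% to 95% of time-outs are imputed below 300 s. Imputation constrained to lie above 300 s recovers the true mean, slope and correlation in every setting.

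**Dependence on the share disqualified.** Fixing the share directly, with the same σ:
- 2%: true mean 132 s, MAR 128–129 s (3 to 4 s too low)
- 5%: 158 s against 148–151 s (7 to 10 s too low)
- 20%: 227 s against 189–198 s (29 to 38 s too low)

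**The case against.** **Disqualified is not the same word as missing.** The coding may follow the cited source or an analysis plan that is not shown. This is a fair caution. But the article assigns no other value and states a general MAR rule, so missing is the natural reading. The clause on best available information leaves room but commits to nothing for the TMT.

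**Associations.** A reader might infer that losing the slow tail weakens the association of cognition with active aging. For regression this does not follow. In complete cases deletion depends only on the predictor, and the slope on log time stays at −0.30; under MAR imputation it is slightly too steep. Only correlations shrink, through the restricted range.

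**The simple remedy.** Entering 300 s for every time-out inflates the slope about as much as MAR imputation, or more. It is not a sound default when TMT is a predictor.

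**The four-error rule.** Because the examiner corrects errors while time is running, a reader might infer that completed times with four or more errors are valid slow times wrongly deleted. The documents do not settle this. Whether a heavily corrected time still measures the construct is a scoring judgement.

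**The contrast with SPPB and audiometry is loose.** One is an ordinal score with a defined zero, the other a value just past a device ceiling. They show that the article elsewhere keeps the poorest performers; they do not show that the TMT rule is wrong.

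**Reach.** A reader might also infer that the cohort comparison suffers. It does not: Table 1 shows no TMT in the historic cohort. TMT is one of five cognitive tests and is not a main outcome of the cross-sectional part. This limits the weight of the point.

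**Conclusion.** The point holds for time-outs. Followed as written, the two rules treat as MAR a value that is missing because of its own size, and they discard the fact that it exceeds 300 s. Mean TMT time and its spread are understated and correlations shrink, more so where time-outs are more frequent. Slopes on log time are unbiased in complete cases and modestly inflated under MAR imputation.

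The direction for mean and spread was the same in every setting tried. The size rests on the assumed log-normal shape, log SD 0.45 and the unknown share disqualified: negligible to small at 2%, and 18 to 24 s in the mean at about 13%. The effect is confined to TMT-A, TMT-B and B/A as descriptors or predictors. This is a moderate point, worth correcting because the correction is cheap.

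**What to change.** - State that a TMT time-out is an informative result, right-censored at 300 s. When TMT is a predictor, use a likelihood or imputation model constrained to values above 300 s. When TMT is the outcome, use a censored regression model. A worst-rank or not-completed category is a simpler alternative. Do not treat time-outs as MAR-missing or as a plain value of 300 s.
- Reserve FIML and imputation under MAR for tests not done for reasons unrelated to cognition.
- Record the time and error count of completed tests with four or more errors, so that the error rule can be examined in a sensitivity analysis. Settle this during data collection, because times that were not recorded cannot be recovered later.
- Report the number disqualified by age group, separately for the time limit and the error rule.

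The cost is slightly more coding and analysis work. Nothing changes for participants.

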#### Physical health

Information on self-reported physician diagnosed chronic diseases is collected during the home interview by prompting participants with ten categories of chronic conditions and then specifying the condition. Listed are: respiratory conditions (asthma, chronic obstructive pulmonary disease, chronic bronchitis, other), cardiac conditions (myocardial infarction, coronary heart disease, heart failure, atrial fibrillation or other arrhythmias, other), vascular conditions (hypertension, thrombosis or intermittent claudication, other), cerebrovascular condition or brain injury (stroke or cerebral infarction, brain injury, other), musculoskeletal condition (rheumatic arthritis, osteoarthritis, chronic back pain or problems, chronic neck pain or problems, osteoporosis, other), visual or auditory impairment (cataract, not surgically repaired, glaucoma, macular degeneration, hearing disorder, hearing injury or other hearing debilitating condition), diabetes mellitus, malignant cancer, neurological condition (Parkinson’s disease, Alzheimer or dementia, epilepsy, other), and depression. Furthermore, an open-ended question about any other physician diagnosed chronic conditions is used. A nurse will categorize the other conditions listed, after which a morbidity index will be calculated similar to one previously used [27]. For some conditions, follow-up questions are asked to ensure safe participation in the physical tests and to form the basis for the clinical examination in the research center. These questions are: pain and symptoms in case of a respiratory condition and/or a cardiac condition, type of surgery in case of coronary heart disease, pacemaker in case of arrhythmias, the type (I or II) and use of medication in case of diabetes mellitus, and the phase of cancer treatment in case of cancer. Finally, questions concerning the presence of severe pain in the back, knees, hips or other locations which hinder daily life, fractures and hospital admissions in the previous year are queried.

Participants are asked to report all medication prescribed by a physician in the postal questionnaire and to indicate whether they use the medication regularly or occasionally. Medication will be categorized [89] and medication potentially affecting cardiac autonomic modulation will be identified.

Clinical health examinations by a research nurse and a physician are organized in the research center for assessing health status and ensuring safety of participants during the physical assessments. The clinical examination includes a review of self-reported chronic conditions and medical prescriptions, current symptoms, blood samples, a resting ECG, and an orthostatic test. If necessary, also glucose levels and oxygen saturation in the blood can be measured by the physician. Because the functional assessments are not more straining than daily life, exclusion from tests is considered case by case.

Blood samples are drawn prior to the health examination in the research center. C-reactive protein levels are determined to ensure safe participation in the physical assessments. Other blood markers include a small blood count, total cholesterol, HDL and LDL cholesterol, and vitamin D. Blood samples will be destroyed once these markers have been determined.

Resting ECG is recorded for ensuring safety of participating in the functional assessments in the research center. Standard 12-lead ECG is recorded after a minimum of 5 min of supine rest and electronically stored (CardioSoft V6.73, GE Healthcare, Chicago, IL, USA). Following the supine rest, an active orthostatic test is performed to assess cardiovascular responses to orthostasis and to study orthostatic tolerance to ensure safety of participants during physical assessments. Having lied down for at least 10 min, the participant stands up and then quietly stands for 6 min. Possible clinical symptoms, such as light-headedness, dizziness or syncope are recorded [90]. Blood pressure is measured during supine rest 1 min before standing up, and again immediately after standing up, and three and 5 min after standing up. Orthostatic heart rate and heart rate variability is assessed using continuous ECG recording starting at 5 min before standing up until 6 min after standing up.

Arterial stiffness, which is an important predictor of cardiovascular disease [91], is measured by the method of pulse wave analysis using the Diagnostic Station DS20 (Schiller AG, Baar, Switzerland). The DS20 is a non-invasive cuff-based device capturing brachial blood pressure and pulse wave forms to estimate the central aortic hemodynamics and pulse wave velocity. After resting in a seated position for at least 10 min to ensure hemodynamic stability, measurements are performed on the dominant arm with the arm positioned on a table so that the middle of the cuff on the upper arm is at the level of the heart. Participants are instructed to refrain from talking and to sit with their back resting against the chair backrest, their feet flat on the floor, and their legs uncrossed. Three measurements per participant with a one-minute rest in between measurements are performed. Each measurement starts with a recording of brachial blood pressure followed by a pulse wave recording with the cuff inflated at the diastolic blood pressure level. Ten stable consecutive pulses are filtered and averaged by the device to calculate the central aortic pulse wave. Evaluation of shape and amplitude of the wave results in the following indirect measures of arterial stiffness (among others): pulse wave velocity, augmentation pressure, and augmentation index [92]. Pulse wave velocity is an estimate of the speed of the pressure wave traveling along the aortic and aorto-iliac pathway [93]. Augmentation pressure and augmentations index are both derived from the ascent of the aortic pressure waveform in late systole attributed to the early return of pulse wave reflection from peripheral sites [94, 95]. Due to heart rate dependency augmentation index is normalized at a heart rate of 75 beats per minute [96]. Blood pressure is measured in conjunction with the arterial stiffness assessment.

Objective anthropometric measurements are taken in the research center. Body height is measured while the participant is standing in an upright position on a stadiometer. Two consecutive measures are taken and the final result, recorded to the nearest 0.5 cm, is the mean of the two values. Body weight is measured in light clothing while the participant stands on an electric scale (Seca, Hamburg, Germany). Weight is recorded to the nearest 0.1 kg. Body mass index will be calculated as weight in kilograms divided by height squared in meters (kg/m^2^). Waist circumference is measured according to the instructions of the World Health Organization [97]. The measurement site is the midpoint between the lowest palpable rib and the top of the iliac crest [97]. Three consecutive measures are taken from the bare skin at the end of an exhalation. The mean of the three values will be recorded as the final result. Multi-frequency bioelectrical impedance measurement (InBody 720, Biospace, Seoul, Korea) provides information on body composition, that is, e.g. body fat mass, lean body mass and its distribution in the body. Measurements are performed according to the instructions of the manufacturer with participants wearing light clothing and standing barefoot on the device and holding the handles in both hands. Cases of non-removable metal jewelry or metal in the body are recorded. Participants with a pacemaker are excluded from the bioimpedance measurement.

Physical frailty phenotype will be determined according to the criteria by Fried et al. [98]. Physical frailty phenotype indicators are: self-reported unintentional weight loss of > 5 kg in the past year (question 1 from SCREEN II-AB questionnaire [99]), exhaustion (questions seven and twenty of CES-D Scale [21]), and low physical activity (self-reporting only light physical activity or less [36, 100]), weakness (lowest quintile of handgrip strength from hand-held dynamometer in their own sex and age group), slowness (lowest quintile of three-meter normal walking speed in their own sex and age group). Frailty status is defined as no frailty (no indicators present), pre-frailty (one to two indicators), and frailty (≥3 indicators) [98].

